### Cost-effectiveness

The estimated impact of formal care input on QoL can be seen as the marginal change in utility (ie, marginal utility $u_{k}$) arising from a marginal change in formal care input k. Care input can be measured as cost-weighted services (eg, hours of home care multiplied by gross unit costs $c_{k}$), allowing the estimation of incremental cost-effectiveness ratios, as marginal costs per marginal utility ($c_{k}/u_{k}$). Incremental cost-effectiveness ratios can be compared between different levels of care intensity, with lower values representing greater efficiency (ie, better value for money). This is relevant for informing policy questions, such as how much potential gain additional funding can achieve or how best to allocate limited budgets across different alternative services.

We also position unpaid carers as beneficiaries of care and consider the cost-effectiveness of LTC services for unpaid carers. This expands the literature on the ‘spillover effects’ of LTC services on carers to consider that services can be targeted ‘at’ or ‘for’ carers and/or jointly for supported people and their carers, based on the whole family (sometimes, known as the ‘dyadic’) approach. See the next section for more details.

Additional considerations that would generalise cost-effectiveness implications are on the interdependency between the health and LTC systems. Existing research has explored, for example, the impact of LTC spending on health service use,^44^ and our stakeholder consultation also revealed an interest in these associated effects. We will assess the effects of LTC provision on avoidable hospitalisations (ie, effects on demand for healthcare) in the analysis. However, we gave these aspects less focus, as we regard them as additional to the main aims of LTC, which is to improve the social care-related QoL of care recipients and their carers.

Differential effects between care alternatives (eg, modes of domiciliary care or care settings) will be captured by the coefficient of the (binary) ‘treatment’ variable (eg, the setting or mode of interest over an alternative) in the matching models. These coefficients will provide the average difference between the ‘treated’ groups’ actual QoL and their QoL if they would have received the alternative type of care (ie, the average treatment effect on the treated).

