## Methods and analysis

This study will involve primary data collection of cross-sectional data that will be analysed using a ‘production function’ approach in which care outcomes (eg, social care-related QoL) are modelled as resulting from care inputs (eg, hours of care per week) and other observable factors.^13 14^

The attribution of causal effects is a challenge, as observed levels and types of care services (ie, the treatment) are dependent on both observable factors as well as factors that cannot be observed or measured; see Gousia *et al*^11^ for a review. Unobserved factors can deviate the study findings from the truth. Randomised control trials (RCTs), in which participants are randomly assigned to prespecified and controlled treatments, are considered the *gold standard* in the economic evaluation of health interventions. The adequate use of randomisation addresses this issue by balancing for observed and unobserved confounders between intervention and control groups.^26^

RCTs have been used in LTC to assess the effectiveness of smaller interventions (eg, home adaptations). For example, using the fact that people referred for the provision of an accessible showering facility by their local authority were usually put on waiting lists (control group), Whitehead and colleagues^27^ designed an RCT by randomly assigning people to receive the adaptation through a fast-tracked process (treatment group).

RCTs are, however, not always feasible or the most appropriate methodology in LTC care due to research ethics as well as internal and external validity considerations. For example, for assessing the comparative cost-effectiveness for domiciliary care by level of care need, we would have to randomly assign packages of different care intensities to people with different levels of care needs, which would be unethical. On the other hand, randomly assigning people with similar care needs to different models of care delivery would not only go against the personalisation approach in LTC in England (mandated by the Care Act 2014) but may also affect the RCT’s internal validity. People usually have strong preferences about their care, and their care arrangements can affect their QoL (eg, control over daily life is one of the domains assessed by the Adult Social Care Outcomes Toolkit (ASCOT)). Moreover, due to the complex and continuing nature of LTC, experimental settings often differ from routine practice, with substantial limitations to external validity.

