### Data requirements

The selected primary *care outcome* measure for people accessing care and for their unpaid carers is the ASCOT interview version (ASCOT-INT4; Netten *et al*; Malley *et al*; Malley *et al*^28^,^30^) and ASCOT-Carer INT4,^31^ respectively. These are validated instruments capturing domains of QoL that are relevant and important to adults accessing LTC services and their carers. The domains were developed based on evidence from qualitative interviews, focus groups and literature review of studies with adults accessing care and their carers to understand people’s views and perspectives on the most important areas of QoL affected by LTC.^28 31 32^ This concept/construct is known as social care-related QoL, which has been found to be sensitive to differences in satisfaction, quality and intensity of care.^33^,^36^ ASCOT has been identified as suitable and recommended for use in economic evaluation of LTC^37^ and is one of two outcome measures recommended by the National Institute for Health and Care Excellence (NICE) guidelines in LTC.^38^ An additional benefit of the use of ASCOT INT4 is that it allows the counterfactual self-estimation of the QoL effect of LTC services, as the difference between the current QoL and the ‘expected’ QoL in the hypothetical situation of absence of services.^30^

In addition to ASCOT, we will also collect data on other outcome measures. This includes potentially avoidable hospitalisations to capture the effects of homecare on avoidance of safety incidents or adverse health outcomes linked to increased demand on the NHS. For carers, we also collect data on self-reported health and employment outcomes.

Information on *care inputs* will be collected using questions on the participants’ use of paid domiciliary care (ie, hours of care per week) and other community-based care services (eg, day care, meals at home, support groups), as well as unpaid care (ie, hours of unpaid care per week).

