### Inclusion criteria

Care recipients must be adults (ie, 18 years or over), accessing domiciliary care through a homecare agency or housing with care scheme (eg, extra care housing) or by employing a PA in England. Unpaid carers must be adult family members, partners or friends supporting a care recipient participating in the study.

All participants must have the mental capacity to consent. Our approach to mental capacity is informed by the following Mental Capacity Act principles: (1) every adult has the right to make decisions for themselves, and it must be assumed that they are able to make their own decisions unless it has been shown otherwise and (2) every adult has the right to be supported to make their own decisions. All reasonable help and support should be given to assist a person to make their own decisions and communicate those decisions before it can be assumed that they have lost capacity.

Our intention is to be as inclusive as possible in relation to people’s abilities and needs; however, we will instruct care providers to exclude people who lack the mental capacity to consent, based on their records of LTC assessment, having a court-appointed deputy or being under a Deprivation of Liberty Safeguard. We will also exclude PA employers who have an additional nominated adult (eg, a legal guardian) on their employer liability insurance.

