### Data analysis

We will conduct separate cost-effectiveness analyses of domiciliary care across levels of care need (or care intensity), types of domiciliary care (eg, homecare agencies vs direct employment of PAs) and care settings (ie, domiciliary care vs housing with care vs care home services).

As mentioned earlier, we will adopt a ‘production function’ approach to estimate the cost-effectiveness of domiciliary care and use IV to address potential selection bias of care intensity with respect to unobserved factors.^13 14^

The IV method can be understood as a two-stage process. The first stage models the endogenous independent variable (ie, in our case, formal care inputs) as a function of so-called instruments and other observed characteristics. The second stage then models the outcome variable (ie, QoL) as a function of predicted values from the first stage model and the observed characteristics. Under the assumptions that the instruments are unrelated to unobserved confounders and enter the second-stage model only via the independent variable of interest (ie, affect care recipients’ QoL only through the formal care services), estimates will give the unbiased causal effect.^40^

The challenge of the IV method is to find ‘good’ instruments, namely variables (highly) correlated with care recipients’ formal care but otherwise unrelated to their QoL and other outcomes of interest. An instrument that worked well in previous studies relies on variation in local authorities’ LTC policy.^13 14^ Local authorities in England have a significant degree of autonomy in designing and commissioning LTC services tailored to population needs and local market circumstances. They also differ in the level of financial resources available to them through externally determined central government grants and council tax (ie, a tax on housing) revenue. As a result, commissioning can often differ between local authorities, and two people with the same care needs and circumstances but residing in different local areas can receive different levels of support.^13 14^ To leverage this policy variation, the above studies specified the leave-one-out average level of formal care input among individuals in a local area as the IV. This measure, also known as a spatial lag, relies on correlation between individuals’ formal care use and the level of care in their local area and is expected to be uncorrelated with unobserved individual-level confounders.

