An alternative to the production function approach for identifying the impact of LTC services on care recipients’ QoL applies a counterfactual self-estimation method. ASCOT-INT4 asks participants to report both their QoL at the time of survey but also their ‘expected’ QoL in the hypothetical situation in which they would not have access to LTC services. This allows the calculation of self-reported QoL gain (ie, impact of services). Although subject to its own limitations, the methodology has been shown to be feasible and to provide similar estimates to the IV method.^30^ Therefore, where possible, we will compare these results to those of the IV analysis. Ideally, where cost-effectiveness estimates using both approaches coincide, this could provide evidence of the robustness of our findings. Where estimates differ, the direction and size of the discrepancy can also be assessed to further understand the limitations of the two approaches.

For comparative cost-effectiveness analysis between care settings, the most common approach to address the issue of self-selection bias is using matching techniques like, for example, Propensity Score Matching.^24 41 42^ By matching individuals with similar observed characteristics from the two groups (eg, gender, age, ethnicity, underlying health issues and difficulty with ADLs), the differential effect of the care services on care recipients’ QoL can be identified if assignment to groups is random conditional on controls.^43^

The same matching technique can be used for the comparative analysis between modes of domiciliary care.

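### Homecare versus care home: families' unpaid care can raise the measured QoL at home, but the only costing described covers formal services

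*Protocol article*

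**What the plan says.** **Unpaid care is an input.** The Methods and analysis section says that outcomes "are modelled as resulting from care inputs (eg, hours of care per week) and other observable factors". The Data requirements section lists what counts as an input: paid domiciliary care, other community services, "as well as unpaid care (ie, hours of unpaid care per week".

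**Treatment and cost are formal only.** The Data analysis section defines "the endogenous independent variable (ie, in our case, formal care inputs". The Cost-effectiveness section takes the QoL effect as the one "arising from a marginal change in formal care input k" and describes costing as "Care input can be measured as cost-weighted services (eg, hours of home care multiplied by gross unit costs". No section puts a value on an unpaid hour, and none fixes a cost perspective.

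**The setting contrast is a matched QoL difference.** Differential effects between settings "will be captured by the coefficient of the (binary) ‘treatment’ variable" in the matching models, read as the average effect on the treated group. The matching is described thus: "By matching individuals with similar observed characteristics from the two groups (eg, gender, age, ethnicity, underlying health issues and difficulty with ADLs". Unpaid hours are not among these examples.

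**Carers come from the domiciliary side.** The Inclusion criteria state: "Unpaid carers must be adult family members, partners or friends supporting a care recipient participating in the study". Care-home data come from an existing dataset (Data requirements), and the Impact on unpaid carers section keeps carer results apart from those of care recipients.

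**The concern.** By the article's own model, unpaid hours help to produce QoL at home. The matched setting effect compares QoL as measured, whatever produced it. If the cost side then counts only formal services, the family's contribution stays in the effect while its hours stay out of the cost.

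The carer analysis does not bring the family back into this comparison. The recruitment described yields carers of people at home and no carers of care-home residents, so family burden cannot be contrasted between settings.

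The stated audience makes this relevant. The Introduction wants to help self-funders and their families to choose between care options, the Aims and objectives refer to effects on society beyond the care recipient, and the Discussion hopes to support families' decisions. A comparison on formal cost alone does not answer the family's question.

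**Working it through.** The article gives no unit cost, no unpaid hours and no cost-effectiveness ratio, so there is no stated figure to reproduce. All values below are assumptions used to show scale.

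**Notation.** Hf and Hu are weekly formal and unpaid hours at home. Hu' is weekly unpaid hours for a care-home resident. c is the formal unit cost, w the value of an unpaid hour, and C the weekly formal cost of a care home.

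**1. Total homecare cost.** Full cost / formal cost = 1 + (Hu/Hf) × (w/c). With w/c = 0.5:
- Hu/Hf = 0.5: 1 + 0.5 × 0.5 = 1.25
- Hu/Hf = 1: 1 + 1 × 0.5 = 1.5
- Hu/Hf = 2: 1 + 2 × 0.5 = 2.0

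With w/c = 1.0 and Hu/Hf = 2 the factor is 3.0; with no unpaid hours it is 1.0.

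**2. Cost difference between settings.** On formal cost, homecare minus care home is Hf·c − C. With unpaid care valued on both sides it is (Hf·c + Hu·w) − (C + Hu'·w). The change is w × (Hu − Hu'). It counts against homecare if Hu > Hu', vanishes if they are equal, and favours homecare if Hu < Hu'. The direction therefore depends on families giving more hours at home than in a care home, which the article does not state.

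**3. A saving does not scale by the factor in step 1.** Take assumed formal costs of 100 at home and 200 in a care home, with Hu' = 0. The formal saving is 100. With home cost × 1.25 it is 200 − 125 = 75; with home cost × 2.0 it is 200 − 200 = 0.

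**4. The marginal ratio behaves differently.** Let s be the unpaid hours displaced by one extra formal hour, and let g and b be the QoL effects of an unpaid and a formal hour.
- Cost per extra formal hour, with unpaid care valued / formal only = 1 − s × (w/c). For s = 0.5 and w/c = 1.0 this is 0.5; for s = −0.25 and w/c = 1.0 it is 1.25.
- QoL effect of formal care, unadjusted / adjusted for unpaid hours = 1 − s × (g/b). For s = 0.5 and g/b = 1.0 this is 0.5; for s = −0.25 and g/b = 1.0 it is 1.25.

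If formal care displaces unpaid care (s > 0), the unadjusted QoL effect is too low and the omitted cost is a saving. Both make formal homecare look worse, the opposite of the direction in step 2 when Hu > Hu'.

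**5. Room for a low-unpaid-hours subgroup.** The Sample size calculations section requires 226 per group for the care-home comparison and targets 800 homecare recipients over three need levels. An even split (assumed) gives 800/3 ≈ 267 with high needs. Excluding more than 1 − 226/267 ≈ 15% of them takes the subgroup below 226.

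**The case against.** **Formal-only costing is a legitimate choice.** The Cost-effectiveness and Discussion sections ask how extra funding or a fixed budget should be used, and the Discussion says that this matches what policy stakeholders and the funder want. Family burden is captured as carer QoL, health and employment, with reasons given for analysing it separately. This stands: the formal-cost result is valid as a public-budget figure, and adding carer QoL loss on top of a replacement cost could count the same burden twice.

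**Detail may sit in a fuller plan.** The matching variables and the costing are given as examples, so unpaid hours may enter the models. This stands as far as the models go, and their absence from the examples is not the point here. It settles less on the cost side, because which resources count as cost determines what the setting comparison estimates.

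**Stronger readings that the article does not support.**
- A reader might infer that the cost-effectiveness ratio itself credits homecare with QoL supplied by families. It does not: its denominator is the effect of a marginal change in formal care. Unpaid care enters only if it moves with formal care or with the instrument and is not adjusted for, and the bias can then run either way.
- A reader might infer that the care-home dataset holds nothing on unpaid care. The variables named are only examples, and the questionnaires are said to be aligned with that dataset.
- A reader might extend the point to agency care versus directly employed personal assistants. Carers of both groups are invited, and carer comparisons between forms of domiciliary care are announced, so carer burden is not lost there.

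**Conclusion.** The point holds for homecare versus care home only. The matched effect is a difference in total QoL, unpaid care contributes to that QoL at home, the costing described is formal, and the carer analysis has no care-home counterpart under the recruitment described. A formal-cost-only comparison then favours homecare from a family or societal viewpoint, on the condition that families give more care at home than in a care home.

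The size is not derivable from the article. The 1.25 to 2.0 factor rests on assumed unpaid hours of 0.5 to 2 times paid hours, valued at half the paid unit cost. It applies to total homecare cost and to nothing else. It would be wrong to conclude that every homecare result is biased in one direction or by that factor. This is a worthwhile and inexpensive improvement; the public-budget analysis is not invalidated.

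**What to change.** - State that results on formal cost take the public-budget perspective.
- Report the homecare versus care-home comparison a second time, with the unpaid hours already collected added at a stated replacement cost and varied over a range. Take care-home unpaid hours from the care-home dataset if recorded there; otherwise vary them from zero upward.
- Do not add carer QoL loss to that same figure. Keep the carer results separate, as planned.
- Treat any subgroup with few unpaid hours, or any balancing on unpaid hours, as exploratory. Setting or mode may itself change unpaid hours, so conditioning on them may remove part of the effect, and the subgroup may fall below 226.

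The cost is a little extra analysis and an assumed value per unpaid hour, which the range makes visible. No new recruitment or survey question is needed.

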**Ethics and dissemination:**

The study received ethical approval from the School of Social Sciences Staff Review Committee at the University of Kent on 20 May 2025 (reference 1195) and the Health Research Authority, London—Camberwell St Giles Research Ethics Committee on 28 October 2025 (reference 25/LO/0652). Implications around consent, data protection and confidentiality, risk and participant payment are discussed. In addition to academic outputs (eg, academic articles, conference presentations), we aim to coproduce news items and blogs with people with lived experience of accessing long-term care and jointly present findings at events aimed at the care sector. Moreover, we will offer participating care providers benchmarking briefs based on our findings.

STRENGTHS AND LIMITATIONS OF THIS STUDYCodesigning survey materials with experts by experience and offering different survey response options to participants (ie, online, post, telephone, face-to-face) to facilitate more inclusive research.Measuring care outcomes using a validated quality of life measure recommended by the National Institute for Health and Care Excellence, allowing the expression of the effectiveness of different long-term care services in terms of quality-adjusted life years.Recruiting people accessing homecare and housing with care from four geographic regions (covering about 30 local authorities) and direct employers of personal assistants from all of England to ensure national representation.Facing the risk of not achieving a sufficiently large sample, despite a comprehensive strategy to avoid a low survey response rate, which could affect the identification of statistically significant differences in cost-effectiveness.The instrumental variable approach to infer causal effects of care services on outcomes in observational studies, although having worked well in previous research, is known to be sensitive to the instrument specification.

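### Reading a lower c_k/u_k as better value, with no condition on the sign of u_k, ranks a care level with a negative estimated effect first; the pairing of unit cost and input unit also needs stating

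*Protocol article*

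**What the plan says.** The Cost-effectiveness section of the protocol article defines u_k as the change in utility "arising from a marginal change in formal care input k". On the scale of the input it says: "Care input can be measured as cost-weighted services (eg, hours of home care multiplied by gross unit costs"), the unit cost being denoted c_k. The ratio that is to follow from this is described by the words "allowing the estimation of incremental cost-effectiveness ratios, as marginal costs per marginal utility" and is given the symbol c_k/u_k. These ratios may then be compared between levels of care intensity, "with lower values representing greater efficiency (ie, better value for money"). The section gives no rule for an estimate of u_k at or below zero and no time unit for the ratio.

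The Data requirements section collects the input through "questions on the participants’ use of paid domiciliary care (ie, hours of care per week"). The strengths and limitations list in the abstract says that the outcome measure allows effectiveness to be expressed "in terms of quality-adjusted life years". The Data analysis section plans separate analyses across levels of need or intensity and uses IV for care intensity. The Sample size calculations section allows for three need levels among 800 homecare recipients and concedes that the subgroup sizes cannot be controlled.

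**The concern.** A ratio with an estimated effect in its denominator orders alternatives properly only while that effect is positive. Here the effect is an IV slope, an imprecise quantity, and it may be estimated within subgroups. If one level yields a negative slope, the stated reading places it above every level where care appears to help.

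The second difficulty is one of units. If the input is already in pounds, u_k is QoL per pound and the unit cost is inside it. Dividing c_k by that u_k uses the unit cost a second time.

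The Discussion intends these comparisons for public budget setting, commissioning and individual choice between services, so a ranking that can invert is worth repairing before the analysis.

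**Working it through.** The document reports no value of c_k, u_k or the ratio, so there is no figure of its own to reproduce. From the document: SD of QoL 0.189, 800 homecare recipients, three need levels. Assumed for illustration: unit costs of £20 to £30 per hour, the slopes, an SD of 10 weekly hours, an even split (800/3 ≈ 267) and the first-stage partial R².

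**1. Sign.** Take c = £20 per hour and three levels:

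| u (QoL per weekly hour) | c/u | u/c (QoL per pound) |
|---|---|---|
| 0.008 | 2,500 | 0.00040 |
| 0.003 | 6,667 | 0.00015 |
| −0.001 | −20,000 | −0.00005 |

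The lowest c/u belongs to the level where care appears to harm. Ranking on u/c puts that level last. The ratio is also discontinuous: with c = £25, u = +0.0001 gives +250,000 and u = −0.0001 gives −250,000. Two nearly identical estimates fall at opposite ends of the ranking.

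**2. How often an estimate might be negative.** Assume separate IV fits and a true slope b = 0.005 per weekly hour, which is 0.05 QoL per SD of hours (0.005 × 10).

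- SE = 0.189 / (10 × √(267 × R²))
- P(negative) = Φ(−b/SE)
- P(at least one of three) = 1 − (1 − P)³, treating strata as independent

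| Partial R² | SE | One stratum | At least one of three |
|---|---|---|---|
| 0.02 | 0.0082 | 27% | 61% |
| 0.05 | 0.0052 | 17% | 42% |
| 0.10 | 0.0037 | 9% | 24% |
| 0.20 | 0.0026 | 3% | 8% |

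Over the same R² range, a slope of 0.002 gives 40% to 22% per stratum, and a slope of 0.010 gives 11% to below 0.1%. This is a normal approximation that ignores clustering, and it is roughest where the first stage is weakest.

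**3. Unit cost.** Let h be weekly hours and Q = a + b·h.

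- Input in hours: u = b, and the ratio is c/b.
- Input in pounds, x = c·h: u = b/c, and the ratio is 1/u = c/b, the same value.
- Literal c/u with input in pounds: c/(b/c) = c²/b, too large by the factor c.

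With c = 20 and b = 0.005, the proper value is 4,000 and the literal one 80,000. Add a second service with c = 30 and b = 0.0076. Its proper value is 30/0.0076 = 3,947, slightly better than 4,000; its literal value is 900/0.0076 = 118,421, clearly worse than 80,000. The order flips. With one common c, every ratio is multiplied by the same constant and the order stands.

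**4. Time basis.** With weekly hours, c/u is pounds per week per unit of QoL, which is coherent. One extra weekly hour held for a year costs 52c and yields u QALYs, so the cost per QALY is 52c/u: for c = 20 and u = 0.005, 52 × 4,000 = 208,000. The constant 52 never changes a ranking.

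**The case against.** The best defence is that the section explains what a cost-effectiveness ratio means for a beneficial input and does not fix a ranking algorithm; handling of negative effects would normally sit in an analysis plan. The Data analysis section also compares IV results, where possible, with self-estimated QoL gain, and the Discussion promises tests of functional form, so an implausible negative slope should be noticed. That is fair, and it lowers the seriousness. It does not remove the point: neither check changes the metric on which levels are compared, and the sentence as it stands gives the wrong order for any negative estimate. Marginal effects by level could also come from one pooled non-linear model, in which case the percentages above do not apply directly.

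Four stronger readings are tempting and are not supported.

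- *The formula is wrong.* Its verbal definition is right, and c_k/u_k is right for hours. The Discussion poses the main question per extra unit of care, with an hour as the example. Cost-weighting is offered as an option. The fault is an unclear pairing of symbol and unit.
- *The result is out by a factor of 52.* The Cost-effectiveness section never calls the ratio a cost per QALY.
- *Costs are left out of the mode and setting comparisons.* The section describes only a QoL coefficient "in the matching models. These coefficients will provide the average difference between the ‘treated’ groups’ actual QoL", but the Data analysis section commits to cost-effectiveness analyses of these contrasts. How the cost difference is estimated is detail that an article leaves to the full plan.
- *Sign changes are likely.* The probabilities run from high to negligible according to inputs that the document does not give.

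**Conclusion.** The point holds as a fault in the stated comparison rule and an ambiguity of units. It is not an arithmetic error in a reported figure. The ranking failure needs no assumption beyond a negative estimate of u_k. Its frequency rests entirely on assumption: about 61% to 8% for at least one negative estimate among three strata, under separate fits, even and independent strata, 0.05 QoL per SD of hours and partial R² of 0.02 to 0.20. The double use of the unit cost follows from the literal text for a cost-weighted input. It inflates the ratio by c_k and can reorder services with different unit costs, but not intensity levels that share one. The design and data collection are unaffected. This merits correction before the analysis, short of an essential change.

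**What to change.** 1. State the input unit and pair it with the ratio: c_k/u_k when the input is in hours, 1/u_k when it is in pounds. State the time basis, and annualise if results are given per QALY (52c_k/u_k for weekly hours).
2. Limit the lower-is-better reading to u_k > 0 with positive incremental cost.
3. Compare levels on marginal QoL gain per pound, or on incremental net monetary benefit over a stated range of thresholds λ (for one weekly hour held for a year, λ·u_k − 52c_k). Both are linear in u_k and behave smoothly through zero.
4. Give uncertainty intervals that remain valid when u_k is near zero, such as Anderson-Rubin or Fieller intervals.

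Ratios should not be withheld because the interval for u_k includes zero. That is a significance filter and would favour exaggerated effects.

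The cost is some wording, a few lines of code, slightly more analysis and a threshold range to state. No new data are needed.
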